## Abstract

**Introduction:**

Cardiovascular and cerebrovascular diseases are projected to expand in the coming decades as the main cause of death. This study outlines the escalating burden of cardiovascular diseases in low‐ and middle‐income countries (LMICs), particularly in Latin America (LA), which is expected to surpass that of other high‐population regions. Despite advances in prevention strategies, adherence to therapeutic goals remains a global challenge, especially in LMICs where control rates are notably low for conditions such as hypertension, type 2 diabetes mellitus (DM2), and dyslipidemia. Emerging evidence from LMICs supports the feasibility and effectiveness of telehealth interventions for cardiometabolic disease management in primary care.

**Aims:**

To address these challenges, a remote chronic disease management program has been developed to optimize risk factor control through standardized medical protocols and task automation.

**Methods:**

This is an open‐label randomized and decentralized clinical trial describing the design and methodology of the TAMIS program, which will assess its impact on community‐dwelling diabetic subjects with uncontrolled HBA1c and uncontrolled LDL‐C and/or blood pressure. Individuals will be randomized to usual care or remote care and followed for 84 weeks. Remote monitoring offers a practical response to the limited capacity of LMIC health systems to ensure sustained follow‐up and continuity of care for chronic conditions. The primary endpoint is a win‐ratio of hierarchical events, including all‐cause deaths and the frequency of all‐cause hospitalizations. The secondary endpoints include control of HbA1c, LDL‐C and blood pressure according to clinical guidelines, as well as patient‐reported outcomes and clinical parameters, including blood pressure, glycemic control, and LDL cholesterol levels. Subgroup analyses will explore the impact of demographics and clinical characteristics on treatment outcomes. Overall, the study aims to improve health care delivery, enhance patient education, and foster collaboration between patients and health care providers to mitigate the growing burden of cardiovascular diseases in LMICs.

## Introduction

1

Cardiovascular and cerebrovascular diseases are projected to become the leading cause of death in low and middle‐income countries (LMICs) by 2040 [1]. Among these nations, Latin America (LA) is expected to surpass both China and India, exhibiting the highest rate of cardiovascular disease‐related deaths per inhabitant [1]. Currently, ischemic heart and cerebrovascular conditions account for nearly 30% of global mortality and an alarming 69% of deaths among individuals aged 20−59 years in Brazil [2, 3]. This trend is particularly concerning as it disproportionately affects individuals in their most productive years, leading to increased morbidity, economic burden, and loss of workforce productivity in LA's adult population [4]. While developed countries have seen a decline in ischemic disease incidence, LMICs continue to struggle with limited health care access, suboptimal preventive strategies, and treatment gaps [5, 6]. Non‐communicable diseases (NCDs) now represent the predominant health challenge in these settings, generating an annual economic impact exceeding 1.2 trillion US dollars [7].

Despite advancements in prevention and treatment, adherence to therapeutic goals remains a major challenge worldwide [8]. Even in high‐income countries such as Canada and Sweden, only about 50% of individuals with type 2 diabetes (DM2), systemic arterial hypertension (SAH), or dyslipidemia achieve proper disease control. In contrast, hypertension control rates in LA remain critically low, ranging from 5% to 8% [8]. In Brazil, these figures are equally concerning, with only 30.6% of individuals achieving target SBP, 18.8% reaching LDL‐C goals, and 41% controlling for HbA1c levels [9].

Traditional interventions such as continuing medical education, patient awareness campaigns, and financial incentives have led to a decline in acute cardiovascular events in developed countries. However, LMICs still face significant obstacles in early diagnosis, treatment accessibility, and long‐term disease management [5, 10].

To bridge these gaps, we have developed the TriAl on the remote Management and control of blood pressure, glycemia, and lipids in a diverse community‐baSed population—Artificial Intelligence platform (TAMIS‐IA), a structured and remotely delivered chronic disease management program. TAMIS‐IA integrates guideline‐based, algorithm‐driven clinical workflows for hypertension, diabetes, and dyslipidemia management. For hypertension, patients perform structured home blood pressure monitoring during 6 consecutive days, with automated calculation of aggregated blood pressure averages guiding predefined titration pathways. For diabetes, remote follow‐up includes structured lifestyle assessment, pharmacologic adjustment according to algorithms based on the American Diabetes Association (ADA) guidelines, and scheduled laboratory reassessments. LDL‐C management follows a stratified risk‐based protocol incorporating laboratory safety parameters and contraindication screening prior to therapeutic escalation. All therapeutic recommendations generated by the system are reviewed and approved by supervising physicians before implementation.

This study will evaluate the clinical impact of TAMIS‐IA on major clinical outcomes, providing valuable evidence on the effectiveness of remote chronic disease management models in LMICs. By leveraging technology‐driven interventions, this trial aims to establish a scalable, cost‐effective, and sustainable strategy for improving long‐term cardiovascular risk management in underserved populations.

## Methods

2

### Trial Design

2.1

This prospective, multi‐center clinical trial aims to evaluate the impact of a remote management program for lipid levels, glucose, and hypertension in Brazilian adults. Eligible participants who meet the inclusion and exclusion criteria will be followed for 84 weeks, with predefined endpoints assessed at specific time points. The flow of patient selection, randomization, and intervention processes is summarized in Figure 1.

**Figure 1 jep70456-fig-0001:**
[figure not shown]
Overview of patient flow and study design.

Participant selection and randomization involve confirming interest, explaining the study details, and assessing eligibility. Baseline demographic data, medical history, and health status will be collected before randomization. During follow‐up visits, the study team will: (i) measure blood pressure and glycemic levels; (ii) administer the study protocol; (iii) monitor symptoms and adverse events, and (iv) evaluate treatment adherence.

Adherence will be defined as the completion of at least 80% of scheduled home measurements and the use of at least 80% of prescribed medication doses during follow‐up. Data will be obtained through the TAMIS‐IA platform and scheduled study visits. Participants meeting both criteria will be classified as adherent in secondary analyses. Low adherence will be addressed through sensitivity analyses.

At baseline and weeks 12, 24, 36, 56, and 84, blood samples will be collected, laboratory tests performed, and study endpoints assessed. At week 84, similar follow‐up procedures will take place, with additional endpoint evaluations and final blood sample collection. In addition to these scheduled in‐person laboratory assessments, follow‐up incorporates structured remote contacts and digital data capture. Participants are not required to attend in‐person visits for each follow‐up interaction. In the intervention arm, counseling and medication titration discussions are conducted remotely by trained monitors under physician supervision. Throughout the study, all data will be systematically documented and entered into a secure database. Additionally, quality of life will be assessed using the European Quality of Life 5 Dimensions (EQ‐5D) and the ICEpop Capability Measure for Adults (ICECAP‐A) at multiple time points. The description of the study procedures and measurements is provided in Supporting Information Material 1: Schedule of Activities and illustrated in Figure 2.

**Figure 2 jep70456-fig-0002:**

Study Schedule.

This trial has been submitted to the Brazilian Registry of Clinical Trials (ReBEC) and registered as a clinical trial under number #15832.

## Participants

3

This will be a multi‐center study enrolling adult patients (≥ 18 years old), regardless of sex, from 20 Basic Health care Units (BHUs) from the Federal District (DF, Brazil). Participants will be randomly selected from the pool of registered diabetic individuals meeting trial eligibility.

### Eligibility Criteria

3.1

Inclusion criteria
i.Adults aged ≥ 18 years, receiving care within the Brazilian Primary Health Care Network.ii.At least one documented consultation with a primary care physician (PCP) within the last 36 months.iii.Ability to provide informed consent personally or via a legally authorized representative.iv.Access to a telephone or digital platform for remote follow‐up.v.Diagnosis of type 2 diabetes mellitus with glycated hemoglobin (HbA1c) ≥ 7.0% measured in a certified laboratory within the previous 18 months.vi.Presence of at least one additional uncontrolled cardiovascular risk factor at baseline:
−Uncontrolled hypertension, and/or−Uncontrolled LDL‐C.

#### Operational Definitions

3.1.1

−Uncontrolled hypertension: mean 24‐h ambulatory blood pressure ≥ 130/80 mmHg, or ≥ 2 office or home BP readings ≥ 130 mmHg systolic and/or ≥ 80 mmHg diastolic recorded in the electronic health record (EHR) within the past 18 months, excluding emergency or procedural visits.−Uncontrolled LDL‐C: (i) LDL‐C ≥ 50 mg/dL in individuals at very high cardiovascular risk; (ii) LDL‐C ≥ 70 mg/dL in individuals at high cardiovascular risk; (iii) LDL‐C ≥ 100 mg/dL in individuals at intermediate cardiovascular risk; (iv) individuals with a history of LDL‐C ≥ 190 mg/dL at any time, according to the 2025 Brazilian Guideline on Dyslipidemias and Atherosclerosis Prevention. Individuals with diabetes mellitus may present cardiovascular risk ranging from intermediate to very high, depending on disease duration, the presence of additional risk factors, or evidence of target‐organ damage.
Exclusion criteria
i.Secondary hypertension or conditions requiring non‐standard management.ii.Participation in another interventional clinical trial.iii.Individuals with active underlying malignancies.iv.Moderate‐to‐severe cognitive impairment or severe psychiatric condition that precludes consent or adherence.v.Inability to use or access a telephone for remote contacts, even with caregiver assistance.vi.Illiteracy that prevents comprehension of informed consent or digital interaction.

The exclusion of illiterate individuals was defined to ensure valid informed consent and reliable participation in remote data collection and digital self‐monitoring. Recruitment occurs in community‐based primary care services serving socioeconomically diverse populations, and results will be interpreted in the context of individuals with functional literacy compatible with digital self‐care within the public health system.

## Ethical Considerations and Good Clinical Practice (GCP) Compliance

4

The study protocol was reviewed and approved by the Research Ethics Committee of the Foundation for Education and Research in Health Sciences (FEPECS), under opinion number 7.348.902, and registered in the national system with the Certificate of Ethical Appreciation Submission (CAAE) number 74170623.0.0000.5553. All participants will provide written informed consent prior to enrollment, in accordance with Brazilian Resolution CNS 466/2012 and international GCP guidelines.

## Interventions

5

Participants in the control arm will receive treatment at the discretion of their physician, without interference from the study personnel, and they will be followed up through app interactions, phone calls, and lab exams every 24 weeks.

Both study arms are recruited and followed within the same BHU of the Brazilian Primary Health Care Network, ensuring comparable clinical settings and multidisciplinary staff. Usual care in these units is provided by PCPs and nurses and is defined as routine management typically involving in‐person consultations every 3–6 months according to clinical need, with medication adjustments and laboratory testing performed at the physician's discretion, and no structured digital follow‐up. In the control arm, no standardized algorithms or automated decision‐support tools are used, and there are no scheduled tele‐touchpoints beyond those required for data collection. All usual‐care contacts and visit frequencies will be documented to allow comparison of exposure intensity between study arms. To minimize contamination between study arms, the structured remote workflow is delivered exclusively by the trained study monitors assigned to the intervention arm. Control participants do not have access to TAMIS‐IA clinical decision support, automated titration protocols, or structured telemonitoring beyond protocol‐required data collection. Usual care providers remain independent from the intervention workflow, and no algorithm‐driven recommendations are integrated into routine care.

Participants in the active intervention arm will receive treatment based on standardized clinical guidelines, with instructions provided remotely by study monitors under physician supervision. The study monitors are health care professionals and research fellows with clinical backgrounds, specifically trained to conduct structured telephone follow‐ups, data collection, and patient education activities. The intervention is supported by TAMIS‐IA, a web‐based digital health platform that enables remote management, patient monitoring, and clinical decision support. All medication adjustments or new prescriptions generated through the digital platform are reviewed and formally approved by physicians before implementation to ensure clinical safety and protocol compliance. Further technical and operational details of the platform are provided in Supporting Information S1: Material 2.

TAMIS‐IA is a non‐commercial digital health platform developed collaboratively by academic and public institutions for research and service improvement. The platform's software and algorithms are maintained under institutional ownership, with no private licensing, profit generation, or commercial partnerships.

All members of the study team involved in follow‐up and data collection underwent structured and standardized training prior to participant contact. The training program included protocol‐based lifestyle counseling focused on weight management, physical activity, sodium reduction, alcohol moderation, and smoking cessation; application of guideline‐directed pharmacologic algorithms for hypertension, diabetes, and dyslipidemia; documentation procedures and data entry within the TAMIS‐IA platform; standardized telephone communication techniques; and identification and reporting of adverse events. Training was delivered by supervising physicians and senior investigators with expertise in cardiovascular and metabolic disease management. Preparatory training sessions were conducted regularly over the year preceding trial initiation through weekly 60‐min meetings focused on protocol familiarization, case discussions, and workflow standardization. Completion of formal training in international GCP, in accordance with International Council for Harmonization (ICH) guidelines, was a prerequisite for participation in study‐related activities. Competency was verified before participant interaction, and ongoing supervision is maintained throughout the trial to ensure protocol adherence and clinical safety.

Data monitoring will be performed remotely by the coordinating center, which maintains a full audit trail of user access, data entry, and edits. Automated consistency checks and range validations are integrated into the electronic data capture platform, and all queries or discrepancies are reviewed and resolved centrally before database lock to ensure data integrity.

Safety assessments are described in Supporting Information Material 3, including the classification, documentation, and reporting of adverse events.

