**Figure 3 jep70456-fig-0003:**
[figure not shown]
Hypertension management algorithm: treatment initiation, titration, and referral pathways. ACEi, angiotensin‐converting enzyme inhibitor; ARB, angiotensin receptor blocker; BP, blood pressure; CCB, calcium channel blocker; CKD, chronic kidney disease; DM, diabetes mellitus; HBPM, home blood pressure monitoring; HCTZ, hydrochlorothiazide.

A customized software platform was developed to automatically calculate weekly BP averages, defining target BP as a weekly systolic BP (SBP) < 130 mmHg and diastolic BP (DBP) < 80 mmHg. The system allows for dynamic adjustments of BP targets based on individual clinical indications.

For patients whose home BP remains elevated, medication adjustments will be conducted remotely, via telephone consultations with a patient monitor, following the clinical algorithm integrated into the software platform. Physicians will review and approve all new prescriptions before implementation. This approach allows for more frequent medication titrations than in standard clinical practice.

After each titration, patients will wait 1 week for stabilization before repeating another 6‐day BP measurement cycle at home. This results in a biweekly cycle of medication titrations, which aligns with the pharmacokinetics of the prescribed antihypertensive agents, including angiotensin‐converting enzyme (ACE) inhibitors, angiotensin‐receptor blockers (ARBs), calcium channel blockers (CCBs), and diuretics.

This accelerated titration protocol aims to overcome the therapeutic inertia commonly seen in traditional BP management. Throughout the study, electrolytes and renal function will be monitored when clinically indicated. Once patients achieve BP control, they will transition out of the intensive titration phase, moving to a surveillance phase with follow‐ups every 6 months.

If a participant's home BP remains elevated despite the use of three antihypertensive agents, including a diuretic, they will be classified as having resistant hypertension and automatically referred to a SAH specialist for further evaluation and treatment.

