**Figure 4 jep70456-fig-0004:**
[figure not shown]
Diabetes management algorithm: stratification, treatment, and monitoring strategies. *If eGFR is adequate. ^Empagliflozin and dapagliflozin have shown benefits in dedicated HF trials. Canagliflozin demonstrated a reduction in HF hospitalization in cardiovascular outcome trials. #Dapagliflozin and canagliflozin showed benefits in kidney outcome studies. Empagliflozin demonstrated a reduction in CKD progression in cardiovascular outcome studies. + Weight loss is greater with semaglutide > liraglutide > dulaglutide > exenatide > lixisenatide. ASCVD, atherosclerotic cardiovascular disease; CKD, chronic kidney disease; DPP‐4i, dipeptidyl peptidase‐4 inhibitor; eGFR, estimated glomerular filtration rate; GLP‐1 RA, glucagon‐like peptide‐1 receptor agonist; HF, heart failure; HFrEF, HF with reduced ejection fraction; SFU, sulfonylurea; SGLT2i, sodium‐glucose cotransporter‐2 inhibitor; TZD, thiazolidinedione.

Patients diagnosed with diabetes will be monitored every 4−6 weeks by the study team to assess their adherence to lifestyle modifications and pharmacological treatment. Laboratory tests, including HbA1c, fasting glucose, and capillary blood glucose (or continuous glucose monitoring data), will be reviewed every 12 weeks. During the scheduled visit week in which laboratory testing is planned, participants will be instructed to undergo blood sample collection at the designated research laboratory affiliated with the study. Laboratory results are securely shared with patients and monitors, and trained staff record verified values in the study database. Additionally, study monitors will recommend visits to the PCP every 12–24 weeks to screen for signs of neuropathy or polyneuropathy.

All prescriptions will follow a structured protocol, supervised by experienced physicians. Medication doses will be adjusted as needed to ensure patients achieve their glycemic targets, such as HbA1c levels, considering their cardiovascular and renal status. Therapy adjustments will also account for the risk of hypoglycemia, cost‐effectiveness, and patient preferences.

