### Safety Assessments

6.4

Safety assessments will include adverse events, clinical laboratory measurements (chemistry, hematology), and vital signs (systolic and diastolic blood pressure). A complete medical, surgical, and family history will be completed at the randomization visit. All laboratory test results must be evaluated by the investigator as to their clinical significance. Any observations at physical examinations or laboratory values considered by the investigator to be clinically significant should be considered an adverse event.

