## Blinding

8

This study will be conducted as an open‐label trial. However, certain personnel will remain blinded to the randomization process. Specifically, the study sponsor, the independent Data Safety Monitoring Board (DSMB), study administrators, and personnel at the supporting organizations and vendors will be unaware of the allocation sequence.

All study data will be collected at participating sites and entered into the TAMIS‐IA platform, a secure, web‐based electronic data capture platform. Participants will be de‐identified using unique alphanumeric codes, and all data will be managed in compliance with the Brazilian LGPD. Data accuracy will be ensured through double‐entry verification, real‐time audit trails, and predefined data validation rules. Quality assurance activities will include biweekly remote audits, centralized query resolution, and continuous oversight by the Coordinating Center.

An independent DSMB composed of experts in cardiology, clinical trials, epidemiology, and biostatistics will oversee the study's safety and scientific integrity. The DSMB will remain blinded to treatment allocation and will conduct closed‐session interim reviews every 12 weeks, evaluating unblinded data for cumulative adverse events, recruitment metrics, and overall risk‐benefit profile. Predefined stopping criteria for harm, futility, or overwhelming efficacy will guide DSMB recommendations.

On the other hand, patients, study investigators, monitors, and clinical staff at the Health care Units will be aware of the allocation. To mitigate biases, the dataset will be de‐identified after data lock, ensuring that the study medication and treatment allocation are concealed from data analysts and statisticians.

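### Study contact and laboratory review are more frequent in the intervention arm by design, so crude between-arm counts of non-serious and laboratory adverse events are liable to show an artefactual excess under remote care

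*Protocol article*

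**What the plan says.** **Control arm.** Section 5 (Interventions) says of control participants that "they will be followed up through app interactions, phone calls, and lab exams every 24 weeks" and adds that "there are no scheduled tele‐touchpoints beyond those required for data collection". Their ordinary care is "routine management typically involving in‐person consultations every 3–6 months according to clinical need", delivered by their own physicians and nurses.

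**Intervention arm.** Section 5.3 (Glucose Management) says "Patients diagnosed with diabetes will be monitored every 4−6 weeks by the study team", with laboratory results reviewed every 12 weeks. Section 5.2 (Blood Pressure Management) describes remote adjustment for those whose home BP stays high: "This results in a biweekly cycle of medication titrations". Once BP is controlled, follow-up becomes six-monthly.

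**Both arms.** Section 2.1 (Trial Design) places the monitoring of symptoms and adverse events at follow-up visits, without distinguishing the arms. It lists assessments at weeks 12, 24, 36, 56 and 84. That list does not match the 24-weekly control schedule in section 5.

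**Use of adverse events.** Section 6.4 states: "Safety assessments will include adverse events, clinical laboratory measurements (chemistry, hematology), and vital signs". It also makes any laboratory value that the investigator judges clinically significant an adverse event. Section 5 says all staff involved in follow-up were trained to identify and report adverse events. Section 8 (Blinding) has the DSMB meet every 12 weeks, "evaluating unblinded data for cumulative adverse events, recruitment metrics" and the overall risk-benefit profile, with predefined stopping criteria that include harm.

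**The concern.** Transient, non-serious events (dizziness, mild hypoglycaemia, muscle pain) and laboratory abnormalities enter the database only if someone asks or tests. If one arm is asked and tested more often, it will record more of them even when the true rates are equal. The trial is open label, the extra contacts are made by staff trained to report events, and the investigator who judges laboratory values knows the allocation.

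The bias runs against remote care. At stake are the safety conclusion about remotely delivered titration and the risk-benefit picture that the DSMB receives repeatedly during the trial. Later analysis cannot repair this unless each event carries a record of how it came to light. It is therefore a data-collection matter and cannot simply be left to the analysis plan.

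**Working it through.** The article states no adverse-event rate or elicitation ratio, so there is no figure of its own to reproduce. Follow-up is 84 weeks (section 2.1), with 419 participants per arm (section 7).

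**1. Scheduled contacts (84 ÷ interval).** Section 5.3 does not name the arm. It is read here as the intervention workflow, because section 5 denies control participants algorithms and structured telemonitoring.

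- Intervention, glucose contacts: 84/6 = 14 to 84/4 = 21. BP titration calls come on top, but only for participants with uncontrolled BP.
- Control: 3 (weeks 24, 48, 72), 4 if week 84 is added, or 5 on the section 2.1 list.
- Contact ratio: 14/3 to 21/3 = 4.7 to 7.0; 14/4 to 21/4 = 3.5 to 5.3; 14/5 to 21/5 = 2.8 to 4.2.

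**2. Laboratory reviews.** Intervention 84/12 = 7; control 3 to 5. Ratio 7/5 = 1.4 to 7/3 = 2.3.

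**3. Agreement of the control schedules.** Weeks 24, 48, 72 and 84 against weeks 12, 24, 36, 56 and 84: only weeks 24 and 84 appear in both. If the 24-weekly schedule governs, each control gap spans two 12-week DSMB intervals. A given control participant then has no new scheduled contact in about every other interval.

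**4. From contacts to recorded events (illustration; recall is assumed).** Take equal, constant true rates, and let the chance that an event is still reported decay with half-life h weeks, so k = ln 2 / h. For gaps L between contacts, the fraction captured is Σ(1 − e^(−kL)) / (84k).

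For h = 8, k = 0.0866:
- 6-weekly: 14 × (1 − e^(−0.520)) / 7.278 = 0.780.
- Section 2.1 weeks (gaps 12, 12, 12, 20, 28): 3.674 / 7.278 = 0.505.
- Ratio: 0.780 / 0.505 = 1.54.

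| Half-life (weeks) | 4-weekly | 6-weekly | Control, section 2.1 weeks | Control, 24-weekly plus week 84 | Ratio, lowest to highest |
|---|---|---|---|---|---|
| 4 | 0.721 | 0.622 | 0.315 | 0.263 | 1.97 to 2.74 |
| 8 | 0.845 | 0.780 | 0.505 | 0.449 | 1.54 to 1.88 |
| 12 | 0.893 | 0.845 | 0.616 | 0.567 | 1.37 to 1.58 |
| 26 | 0.949 | 0.924 | 0.786 | 0.755 | 1.18 to 1.26 |
| 52 | 0.974 | 0.961 | 0.883 | 0.866 | 1.09 to 1.13 |

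**5. Visibility with 419 per arm (illustration).** Assume a true mean of 0.5 events per person over 84 weeks and 6-weekly intervention contacts. The proportion with at least one recorded event is 1 − e^(−0.5 × captured fraction). At h = 8 this is 0.323 against 0.223 (section 2.1 weeks) or 0.201 (24-weekly plus week 84). The chance of a nominal two-sided p < 0.05 is then 90% to 98%. It is 71% to 88% at h = 12, 28% to 39% at h = 26, and 11% to 15% at h = 52. Chance alone would give 2.5% in that direction.

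**The case against.** The strongest reply is that the article never says adverse events are elicited at the extra contacts. Section 2.1 ties them to follow-up visits in both arms, and the 4- to 6-weekly contacts are made "by the study team to assess their adherence to lifestyle modifications and pharmacological treatment". The detailed rules are assigned to Supporting Information Material 3 and the visit schedule to Material 1. Neither is shown, and they may align the arms. The 24-week interval may qualify only the laboratory tests. Control patients also see their own physicians. Section 5 records contact intensity, and the Discussion admits ascertainment bias. No between-arm test of adverse events is specified.

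Much of this limits the claim. A reader might infer that events are elicited three to seven times as often under remote care, or that recorded events will differ by that factor. Neither is supported. Elicitation at the extra contacts is an inference. An event ratio of 2.8 to 7 merely restates the contact ratio, and arises only if recall stops abruptly after about 4 weeks. Nor does every intervention participant have two-weekly calls, since eligibility allows uncontrolled LDL-C without uncontrolled BP.

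The core remains. Staff trained to report events will hear of them on adherence calls, and section 2.1 itself describes follow-up as including structured remote contacts. Laboratory values can become events whatever a call is for. Usual-care visits add about 3 to 6 occasions (84 weeks is about 19.4 months; divided by 6 and by 3), but section 5.3 also recommends primary-care visits to its patients every 12 to 24 weeks. Recording contact intensity without saying how it will be used does not correct the comparison, and the admitted limitation is put down to open-label design.

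**Conclusion.** The point holds in a limited form and should be addressed. The unequal observation is written into the article: a 2.8- to 7-fold difference in scheduled contacts and 1.4- to 2.3-fold in laboratory reviews. Crude between-arm counts of non-serious and laboratory adverse events are therefore liable to be inflated under remote care. The recorded ratio is not determined by the documents. It is about 1.1 to 1.9 for assumed recall half-lives of 52 down to 8 weeks, and higher if recall is shorter.

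This rests on three assumptions: events that surface at intervention contacts are recorded, true rates are equal, and the unseen supplements do not already align the arms. A real reduction in events could mask the artefact.

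A reader might go further and expect a false harm signal that stops the trial. The article does not support that. It does not say that the harm criteria use non-serious counts, and section 6.1 takes deaths and hospitalizations from health records, discharge summaries and death certificates, so these are largely unaffected.

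**What to change.** 1. Reconcile section 2.1 and section 5 on the control schedule, and state which weeks are common to both arms. Which schedule applies is for the investigators to decide.
2. Record, for each adverse event, the contact or source at which it was found.
3. In sections 6.4 and 8, base the primary between-arm comparison and the comparative DSMB table on events elicited with the same questions and look-back at the common weeks, plus serious events taken from records in both arms. Scheduled elicitation is then equal (for example 5 against 5 if the section 2.1 weeks are confirmed).
4. Also give the DSMB all adverse events by arm, showing separately those found only at intervention-only contacts, so that transient harms during titration stay visible.

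The cost is one CRF field, an additional table, wording in the protocol and DSMB charter, and fewer events in the primary comparative table. If the unseen supplements already contain these rules, a cross-reference in section 6.4 would suffice for items 2 to 4.
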